# Intravenous immunoglobulin and intravenous methylprednisolone as optimal induction treatment in chronic inflammatory demyelinating polyradiculoneuropathy: protocol of an international, randomised, double-blind, placebo-controlled trial (OPTIC)

**DOI:** 10.1186/s13063-021-05083-1

**Published:** 2021-02-19

**Keywords:** Chronic inflammatory demyelinating polyradiculoneuropathy, CIDP, Randomised controlled trial, RCT, Corticosteroids, Methylprednisolone, IVMP, Intravenous immunoglobulins, IVIg

## Abstract

**Background:**

International guidelines recommend either intravenous immunoglobulin (IVIg) or corticosteroids as first-line treatment for chronic inflammatory demyelinating polyradiculoneuropathy (CIDP). IVIg treatment usually leads to rapid improvement and is generally safe, but does not seem to lead to long-term remissions. Corticosteroids act more slowly and are associated with more side effects, but may induce long-term remissions. The hypothesis of this study is that combined IVIg and corticosteroid induction treatment will lead to more frequent long-term remissions than IVIg treatment alone.

**Methods:**

An international, randomised, double-blind, placebo-controlled trial, in adults with ‘probable’ or ‘definite’ CIDP according to the EFNS/PNS 2010 criteria. Three groups of patients are included: (1) treatment naïve, (2) known CIDP patients with a relapse after > 1 year without treatment, and (3) patients with CIDP who improved within 3 months after a single course of IVIg, who subsequently deteriorate at any interval without having received additional treatment. Patients are randomised to receive 7 courses of IVIg and 1000 mg intravenous methylprednisolone (IVMP) (in sodium chloride 0.9%) or IVIg and placebo (sodium chloride 0.9%), every 3 weeks for 18 weeks. IVIg treatment consists of a loading dose of 2 g/kg (over 3–5 days) followed by 6 courses of IVIg 1/g/kg (over 1–2 days). The primary outcome is remission at 1 year, defined as improvement in disability from baseline, sustained between week 18 and week 52 without further treatment. Secondary outcomes include changes in disability, impairment, pain, fatigue, quality of life, care use and costs and (long-term) safety.

**Discussion:**

In case of superiority of the combined treatment, patients will experience the advantages of two proven efficacious treatments, namely rapid improvement due to IVIg and long-term remission due to corticosteroids. Long-term remission would reduce the need for maintenance IVIg treatment and may decrease health care costs. Additionally, we expect that the combined treatment leads to a higher proportion of patients with improvement as some patients who do not respond to IVIg will respond to corticosteroids. Risks of short and long-term additional adverse events of the combined treatment need to be assessed.

**Trial registration:**

ISRCTN registry ISRCTN15893334. Prospectively registered on 12 February 2018.

Role of sponsor {5c}	The sponsor played no role in grant applications, the design, data collection, trial management, data analysis and interpretation. These tasks were the responsibility of the steering committee (see below under 5d). University College London Hospitals (UCLH) are the delegated coordinator in the United Kingdom (UK). This manuscript was written by the authors ({5a}). This manuscript is based on protocol version 3.5.15MAY2020. Decision to submit this manuscript was made by the steering committee. Trial results will be published in an international peer-reviewed journal. The steering committee and writing committee will have full access to data after completion of the trial and will make the final decision to submit the manuscript. Funders have no role in study design, data collection and analysis, decision to publish, or preparation of future manuscript(s).

## Introduction

### Background and rationale {6a}

Chronic inflammatory demyelinating polyradiculoneuropathy (CIDP) is an immune-mediated neuropathy affecting the arms and legs [1, 2]. Treatment of CIDP can be divided into (short-term) induction treatment and (long-term) maintenance treatment. First choice induction treatment recommended by the international European Federation of Neurological Societies/Peripheral Nerve Society (EFNS/PNS) guideline consists of either intravenous immunoglobulin (IVIg) or corticosteroids [3]. Several randomised controlled trials with different designs have demonstrated efficacy of these treatments [4, 5]. In responders, IVIg leads to improvement in most patients within 6 weeks of treatment [6]. Time to improvement with pulsed high-dose corticosteroids is longer, around 3 to 4 months [5]. The more rapid improvement with IVIg as well as the arguably preferential adverse event (AE) profile compared to corticosteroid treatment has made IVIg the first choice for most patients and physicians in the Netherlands, but also in other high-income countries [3, 7]. For the same reasons, IVIg is advocated for more severely affected patients and for long-term maintenance treatment. However, an important advantage of corticosteroids compared to IVIg is that they may lead to long-term remissions, defined as a stable condition without the need for continued treatment [8, 9]. In a recent open-label non-controlled pilot study, 20 CIDP patients were treated with a combination of IVIg and intravenous methylprednisolone (IVMP) over 4 months after which treatment was stopped. The majority of patients who completed the treatment protocol were in remission at 1 year. No patients discontinued treatment due to AEs associated with methylprednisolone [10]. We hypothesise that combining IVIg and pulsed IVMP as induction treatment will lead to more long-term remissions than IVIg monotherapy in patients with CIDP.

## Objectives {7}

The primary objective of this randomised controlled trial is to compare IVMP versus placebo in CIDP patients receiving IVIg and assess whether patients who receive IVMP achieve long-term remission more frequently than patients who receive placebo. The secondary objectives are to assess whether the combination of IVIg and IVMP, compared to IVIg alone, leads to:
More frequent improvementMore rapid improvementMore or less adverse eventsReduced healthcare costs

## Trial design {8}

The OPTIC trial is an international, multicentre, randomised, double-blind, placebo-controlled, parallel group superiority trial with two treatment arms allocated in a 1:1 ratio.

## Methods: participants, interventions and outcomes

### Study setting {9}

The trial will take place in five tertiary neuromuscular centres and three large general neurology departments in the Netherlands as well as six tertiary neuromuscular centres in the United Kingdom (UK). Participating investigators and centres are listed on page 35. The expected inclusion ratio between the Netherlands and the UK is 2:1.

### Eligibility criteria {10}

#### Inclusion criteria

We will include patients of 18 years of age or more with ‘probable’ or ‘definite’ CIDP according to the EFNS/PNS 2010 criteria [3], comprising three patient groups:

Treatment naïvePreviously treated patients who have a relapse* after a remission of at least 1 yearPatients treated with a single loading dose of IVIg in the last 3 months who achieved either a subjective or objective improvement and subsequently had a deterioration as judged by his or her treating physician (for definition of deterioration see paragraph 4.1).

* A relapse or deterioration after treatment is defined as any deterioration warranting treatment as judged by the treating physician.

#### Exclusion criteria

Presence of IgM paraproteinemia and/or anti-MAG antibodies or known CIDP-specific antibodies associated with poor treatment response to IVIgUse of drugs known to cause a demyelinating neuropathyUse of any immunosuppressive or immunomodulatory drugs in previous 6 months (except for a single loading dose of IVIg within 3 months or low dose prednisolone (20 mg or less) for a short period not exceeding 2 weeks)Known serious adverse events (SAEs) with previous IVIg or corticosteroid treatment. Hypersensitivity to methylprednisolone or any component of the formulation. Hypersensitivity to the human immunoglobulins or to any of the excipients. Selective IgA deficiency patients who developed antibodies to IgASystemic fungal infections, unless specific anti-infective therapy is employedKnown hyperprolinaemia type I or II or known fructose intoleranceOne of more of the risk factors associated with increased risk of AEs of IVIg or IVMP or conditions that could lead to unblinding of treatment (i.e. diabetes, IgA deficiency, gastric ulcers, psychosis, severe hypertension (180/110 mmHg or more on repeated measurements), hypocalcaemia (lower than 2.20 mmol/L, corrected for albumin), moderate or severe heart failure, severe cardiovascular disease (i.e. more than one myocardial infarction and or ischemic stroke), renal failure (glomerular filtration rate < 30 ml/min))History of osteoporosis or osteoporotic fracturesKnown active malignancy, currently treated with chemotherapy or immunomodulatory drugs, or with a life expectancy of less than 1 yearBodyweight more than 120 kgPregnancy or nursing mother; intention to become pregnant during the course of the study; female patients of childbearing potential either not using or not willing to use a medically reliable method of contraception for the entire duration of the study. A woman is considered of childbearing potential from menarche and until becoming post-menopausal, unless permanently sterile. Permanent sterilisation methods include hysterectomy, bilateral salpingectomy and bilateral oophorectomy. A postmenopausal state is defined as no menses for 12 months without an alternative medical cause. Acceptable methods of contraception are combined (oestrogen and progestogen containing) hormonal contraception associated with inhibition of ovulation (whether oral, intravaginal or transdermal), progestogen-only hormonal contraception associated with inhibition of ovulation (whether oral, injectable or implantable), progestogen-only oral hormonal contraception, where inhibition of ovulation is not the primary mode of action, male or female condom with or without spermicide, cap or diaphragm, intrauterine device (IUD), intrauterine hormone-releasing system (IUS), bilateral tubal occlusion and vasectomised partner (provided that partner is the sole sexual partner of the trial participant and that the vasectomised partner has received medical assessment of the surgical success)Known cataract or cataract obvious on fundoscopyCurrent psychosis or past history of psychosisPoor dental statusKnown pulmonary embolism or other deep venous thrombosis in patient’s medical history, without current anticoagulant therapyAdults lacking capacity to give informed consent (IC)Lack of written IC

### Who will take informed consent? {26a}

The treating neurologist or an authorised delegate, such as a trained research nurse, obtains IC. After an explanation by the PI or an authorised surrogate and after reading the patient information sheet, patients are asked to consider participation. If necessary, further explanation will be provided.

### Additional consent provisions for collection and use of participant data and biological specimens {26b}

Additional consent is requested to allow for participants to be notified of possible follow-up studies, request relevant contact information and be informed which study treatment they received during the trial. This trial does not involve collecting biological specimens.

### Interventions

Patients will be randomised to receive 7 infusions of 1000 mg IVMP (intervention) or placebo (comparator) in combination with IVIg (standard care), every 3 weeks during the 18-week intervention period (Fig. 1; see the ‘Participant timeline {13}’ section). Both study arms receive IVIg, which consists of a loading dose (2 g/kg divided over 2–5 days) and 6 maintenance treatments of 1 g/kg (given over 1–2 days), as well as weekly alendronic acid 70 mg and daily calcium/vitamin D 500 mg/800 IU (co-medication) to reduce the chance of corticosteroid-induced AEs according to national guidelines [11]. All brands of IVIg are allowed.

**Fig. 1 Fig1:**
[figure not shown]
Treatment protocol and follow-up

#### Explanation for the choice of comparators {6b}

The comparator consists of sodium chloride 0.9% (placebo).

##### Dosage and administration

The dose of sodium chloride 0.9% is 100 ml and will be administered by intravenous infusion. Sodium chloride 0.9% was chosen as comparator treatment as it appears identical to the intervention treatment, which is prepared using a sodium chloride solution. Sodium chloride is widely used as a solvent and it has few side effects. Large amounts of sodium chloride can cause peripheral oedema, hypernatremia and thrombophlebitis. These adverse events are not expected given the small amounts of sodium chloride used in this study (100 ml every 3 weeks). Preparation, labelling and administration are covered under the ‘Intervention description {11a}’ section.

#### Intervention description {11a}

Interventional treatment consists of intravenous methylprednisolone.

##### Dosage and administration

The IVMP dose is 1000 mg in 100 ml sodium chloride 0.9% solution. Venous access and administration of treatment will be provided by hospital nurses or by Sanquin Home Care services. In the Netherlands, the first treatment will be administered in a hospital or day care centre and the remaining infusions in a hospital, day care centre or at home (Sanquin Thuisservice, NL) according to local treatment protocols. In the UK, all treatments will be administered in a hospital. IVMP (or placebo) will be administered during 60 min, prior or after IVIg infusion, depending on logistical preference of participating hospitals and home care services. IVIg and IVMP/placebo may be administered on the same day, but not simultaneously. For each treatment interval, a window of 2 days is accepted for administration of study treatment.

##### Preparation of IVMP and placebo

In the Netherlands, IVMP vials will be provided with a Good Manufacturing Practice (GMP) annex 13 label by the trial pharmacy of the Amsterdam UMC, location AMC (referred to as ‘AMC trial pharmacy’). AMC trial pharmacy will distribute the vials to the pharmacies of the participating hospitals in the Netherlands. Local pharmacies are allowed to order the methylprednisolone, after approval by the Medical Research Ethics Committee (MREC). Pharmacies are allowed to use their sodium chloride 0.9% from stock to prepare the placebo. For administration in the participating centres, IVMP/placebo (or: investigational medical product, IMP) will be prepared and labelled locally. For treatments at home (only in the Netherlands), IMP will be prepared by the AMC trial pharmacy. IMP will be labelled according to GMP (annex 13), in line with the pharmacy manual provided by the AMC trial pharmacy. AMC trial pharmacy and pharmacies of the participating centres will be aware of patient treatment allocation and will dispense accordingly. A second pharmacist will control dispensing of correct dose and treatment allocation. In the UK, pharmacies may use local stock for IMP. Preparation of IMP will be performed by the hospital pharmacist or an (unblinded) nurse, depending on local pharmacy protocols. When IMP preparation and labelling are performed by an unblinded nurse on the ward, a different, blinded nurse will subsequently administer treatment. Study medication, including placebo, will be put into indistinguishable infusion sacks to ensure adequate blinding. Sacks will be labelled according to institutional standard operation procedures (SOP’s) and national guidelines and regulation. At least the following items are present on the label: name of the patient, name of the study, the content (noted as follows to include both IMPs: ‘methylprednisolone 1 gram *or* placebo’, to prevent unblinding) and expiration date. After preparation, study drug and infusion material will be distributed to the departments of the participating centres or to patient’s home address where home-care nurses administer treatment. In the Netherlands, Sanquin Blood Supply will distribute IMPs for home care. AMC trial pharmacy supplies the medication to Mediq pharmacy. For transportation of IMP to patient’s home, infrastructure of Mediq pharmacy in place for IVIg distribution will be used, in line with Good Distribution Practice (GDP). Administration of IVMP has to start within 7 days after preparation (transfer of IVMP solution from to infusion bags/containers) in cooled condition, per summary of product characteristics (SmPC) of IVMP.

#### Criteria for discontinuing or modifying allocated interventions {11b}

Changes in IMP dosing due to potential AEs will not be allowed. Decision to postpone or not administer a single IMP infusion (for example in case of adverse events or new contra-indication to administer IMP) or to discontinue further IMP treatment altogether will be made by the treating physician, if necessary, after deliberation with PI. Any changes in IMP regimen will be discussed with the coordinating PI prior to implementation and recorded as a protocol deviation.

#### Strategies to improve adherence to interventions {11c}

Adherence to intervention protocol is maximised by careful counselling of participants and training of study staff (including home care nurses) and monitored using drug accountability logs. If necessary, training is repeated during the course of the study. All nurses involved in IMP preparation and administration in the UK will undergo Good Clinical Practice (GCP) training and protocol training. Nurses will record the administration date and time of infusion (start to end), infusion speed, blood pressure (before and after) and AEs in a logbook. Blood glucose measurements will not be taken during or directly after an infusion, even if required in local protocols. Logbooks of administration at participating centres will be kept by the local investigator. At the end of individual treatment period, study data will be added to the electronic case report forms (eCRF). Logbooks from the pharmacists, local investigators, and Sanquin Home Care services will be compared with the dispensing sheets of the trial pharmacist after trial has ended and blind has been broken. In the UK, two separate logbooks will be used, one to be completed by the unblinded nurse preparing the drug, and one to be completed by the blinded nurse administering the infusion of IMP.

#### Relevant concomitant care permitted or prohibited during the trial {11d}

The decision to change IVIg treatment regimen (i.e. following adverse events or new contra-indication) or to discontinue IVIg treatment altogether will be made by the treating physician, if necessary, after discussion with PI. Changes will be recorded as a protocol deviation. IMP administration will continue according to protocol regardless of changes in IVIg treatment. Use of any immunosuppressive co-medication 6 months prior to the study is an exclusion criterion. Anti-histamines are frequently used to prevent or reduce skin reactions following IVIg treatment and are allowed during the study. Proton-pump inhibitors (PPI) or H2 antagonists can be used to treat any dyspepsia caused by either steroids, or IVIg, or alendronate. Changes in other co-medication during the study are allowed, as one does not expect this to influence the disease course. Administration of live or live attenuated vaccines is contraindicated in patients receiving immunosuppressive doses of corticosteroids; however, any vaccination is allowed up to 6 weeks before the first study treatment and 6 weeks after the last study treatment.

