### Outcomes {12}

#### Primary outcome

The primary outcome is the number of patients in remission at 52 weeks after start of treatment. Remission is defined as sustained improvement without the need for further treatment. Improvement is defined as improvement by at least the minimal clinical important difference (MCID) on the inflammatory Rasch-Overall Disability Scale (I-RODS) and/or improvement of one or more points on the adjusted Inflammatory Neuropathy Cause and Treatment Disability Scale (INCAT-DS) at 18 weeks (end of treatment) compared to baseline. For the I-RODS, MCID is calculated using a statistical approach in which an increase of 1.96 SE is considered relevant improvement [12]. For the adjusted INCAT-DS, a decrease of 1 point or more is considered a relevant improvement [13, 14]. Changes in upper limb function from ‘0’ (normal) to ‘1’ (minor symptoms) or from ‘1’ to ‘0’ are not considered relevant deterioration or improvement [13]. Sustained is defined as no deterioration between 18 and 52 weeks, i.e. difference on the I-RODS of less than the MCID difference and/or less than one point on the adjusted INCAT-DS. Patients will be considered a treatment failure if they (1) received additional CIDP treatment during the 18-week intervention period, (2) do not improve at 18 weeks, (3) restart CIDP treatment for any reason between 18 and 52 weeks, or (4) do not show a sustained improvement at 52 weeks as defined above.

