### Participant timeline {13}

Total follow-up is 104 weeks (2 years). After the intervention period of 18 weeks, patients will be followed for another 86 weeks during which treatment will be given only in case of deterioration by at least the MCID on the I-RODS and/or deterioration (i.e. increase) of at least one point on the adjusted INCAT-DS. Choice of treatment in case of relapse is at discretion of the treating physician. If a change of treatment regimen is regarded necessary during the 18 weeks’ intervention period, trial medication will be stopped but further follow-up will continue as scheduled. Additional (ad hoc) visits, i.e. if a relapse is suspected, can be scheduled at discretion of treating physician. Treatment protocol and follow-up are illustrated in Fig. 1.

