#### Procedure for unblinding if needed {17b}

Pharmacists will be the only persons able to break the randomisation code. The randomisation code will be broken after the last follow-up visit of the last patient, after data cleaning and database lock. The randomisation code can be broken during the first 18 weeks if unblinding is judged necessary by treating physician to start additional treatment or to change the treatment regimen. These patients will be considered treatment failures and will reach a preliminary endpoint. All secondary outcome measurements will be performed before the blind is broken. In these cases, the coordinating PI will remain blinded. Treatment allocation will not be revealed in patients who are considered a treatment failure, but do not need or do not wish to receive additional treatment.

The randomisation code can be broken if a relation between trial treatment and a SAE is suspected and if knowledge of treatment allocation is deemed necessary by local investigator or treating physician. In case of a Suspected Unexpected Serious Adverse Reaction (SUSAR), the investigator will send an Unblinding Request Form (URF) to the coordinating PI and make every effort to contact the coordinating PI to discuss options. If unblinding is deemed necessary, coordinating PI will send the URF to the study pharmacist. The study pharmacist will reveal treatment allocation of the individual patient to an independent physician on the unblinding form (UF) to ensure continued blinding of local investigator and treating physician. The UF must include the date, time and reason for unblinding. This information will be recorded in the eCRF and local source documents. If the blind is broken, the patient must be discontinued from study medication as soon as possible. The patient will be encouraged to perform an end of study assessment and be under medical supervision until symptoms cease or the condition becomes stable. An independent physician will document the SUSAR in the appropriate Dutch module (ToetsingsOnline) in order to maintain the blind for other research team members.

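### The rules on continuing or stopping trial medication when IVIg is changed in weeks 0–18 overlap without a stated boundary, and the in-treatment failure events are not the same in every section

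*Protocol article*

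**What the plan says.** Both arms receive IVIg as part of the trial regimen. Section Interventions states: "Both study arms receive IVIg, which consists of a loading dose", followed by six maintenance courses.

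Section {11d} gives the treating physician "The decision to change IVIg treatment regimen (i.e. following adverse events or new contra-indication) or to discontinue IVIg treatment altogether". It then says "Changes will be recorded as a protocol deviation", and "IMP administration will continue according to protocol regardless of changes in IVIg treatment".

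Section {13}, directly after sentences on deterioration and on the choice of treatment at relapse, says: "If a change of treatment regimen is regarded necessary during the 18 weeks’ intervention period, trial medication will be stopped". Follow-up continues as scheduled. The sentence names neither a drug nor a reason.

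Section {17b} lets the code be broken in the first 18 weeks "if unblinding is judged necessary by treating physician to start additional treatment or to change the treatment regimen". It declares these patients treatment failures who have reached a preliminary endpoint.

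The primary outcome definition in section {12} has four failure criteria. The only one that concerns a treatment change in the first 18 weeks is the first: "received additional CIDP treatment during the 18-week intervention period". Section {30} likewise names only deterioration that requires additional CIDP treatment as the treatment-change event in that period.

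**The concern.** There are two separate problems.

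The first is exposure. An IVIg change in weeks 0–18 is a change in IVIg treatment, so {11d} keeps the study drug running. It is also, in ordinary language, a change of treatment regimen, so {13} stops it. Where both apply, the number of study-drug infusions the patient receives depends on which section is followed.

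The second is the primary outcome. {17b} treats starting additional treatment and changing the regimen as two distinct reasons for breaking the code, and either one makes the patient a failure. {12} recognises only the first. Nothing says whether an altered IVIg regimen counts as additional CIDP treatment. A patient whose regimen is altered without unblinding can still be counted in remission; one with the same alteration after unblinding cannot. Requesting the code is the physician's decision after randomisation, so it is a poor basis for a primary-outcome classification.

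**Working it through.** The point is textual, so the main check is to run typical cases through each section as worded.

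| Event in weeks 0–18 | Study drug under {11d} | Study drug under {13} | Failure under {12}, criterion 1 | Failure under {17b} |
|---|---|---|---|---|
| IVIg altered for an adverse event | continues | stops if read literally; context points elsewhere | not listed, unless altered IVIg is additional treatment | only if unblinded to make the change |
| IVIg altered because of deterioration | continues (no exception stated) | stops | open: depends on the meaning of additional | only if unblinded |
| IVIg stopped for a contra-indication, switch to another CIDP treatment | continues | stops | open, though a replacement would probably be counted | only if unblinded |
| IVIg unchanged, other CIDP treatment added | silent | stops, if the addition counts as a regimen change | failure | failure if unblinded |

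Rows 2 and 3 meet the wording of both medication rules with opposite results. Row 1 conflicts only on a literal reading. Row 4 shows no conflict. The failure columns do not depend on which medication rule was followed.

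Follow-on effects, from the text:
- Per-protocol set ({20c}): a patient who missed one IVIg course stays in. If study drug is stopped after that course, the allocated treatment was not completed. Most other IVIg changes are deviations that remove the patient either way.
- Adverse events ({22}): the recording window is 24 weeks, but ends 6 weeks after the last study treatment if treatment stops early.

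Scale. Inputs from {14}: remission 35% versus 65%, two-sided 0.05, 80% power, 10% attrition.
- Plan's own figure: n = [1.960 × √(2 × 0.5 × 0.5) + 0.842 × √(0.35 × 0.65 + 0.65 × 0.35)]² / 0.30² = (1.386 + 0.568)² / 0.09 = 42.4, so 43 per arm; 43/0.90 = 47.8, so 48. The stated sample size reproduces and is not in dispute.
- One reclassified patient: 1/48 = 2.1 percentage points of an arm.
- For comparison, with 17/48 remissions in the control arm, 27/48 gives z = 0.2083/√(0.4583 × 0.5417 × 2/48) = 2.05, which is significant; 26/48 gives z = 0.1875/√(0.4479 × 0.5521 × 2/48) = 1.85, which is not. Near the planned control rate, significance needs a difference of about 10 patients.
- Illustration only: suppose a share f of would-be remitters in both arms is reclassified as failures, so the rates become 0.35(1 − f) and 0.65(1 − f). With 48 per arm, power falls from 84.8% to 80.8% (f = 5%), 76.6% (10%) and 67.5% (20%). With 43 per arm it falls from 80.6% to 76.3%, 71.8% and 62.6%. The documents support no particular f.

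**The case against.** The strongest reply is that the two medication rules address different situations. {11d} concerns IVIg alone and names adverse events or contra-indication. {13} follows text on deterioration, and {22} illustrates early stopping by deterioration and a switch to plasmapheresis. On that reading, changes made for tolerability come under one rule and changes made for worsening under the other. This is plausible and disposes of much of row 1. It does not settle rows 2 and 3, because no section states the boundary. The parenthesis in {11d} cannot supply it: the protocol uses i.e. loosely, as in {30}, where a relapse is given after i.e. to illustrate restarting for any reason.

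A second reply is that {11b} requires any change in the study-drug regimen to be discussed with the coordinating PI beforehand. That does limit divergence between sites, but it gives the coordinating PI no rule to apply.

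A third is that few patients will be unblinded to change the regimen without also receiving additional treatment; {17b} itself withholds the allocation from failures who neither need nor want additional treatment. That may well be so. It makes the outcome mismatch narrow, but does not remove it.

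A fourth is that this is a condensed article and the full protocol may draw the line. If it does, the article only needs correcting. Two explicit instructions that overlap are nevertheless more than omitted detail.

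Two stronger readings are tempting. A reader might infer that following {13} rather than {11d} makes the patient a treatment failure. It does not: {13} assigns no failure, {11b} allows the study drug to be discontinued without calling it failure, and failure comes only from {12} or {17b}. A reader might also infer that a material share of each arm, say 5–10% (2.4–4.8 of 48), is affected, and more so in the arm doing worse. The documents give no such rate. Any count of all IVIg changes would include tolerability changes that {11d} covers expressly, and patients who fail anyway through additional CIDP treatment or lack of improvement at week 18.

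**Conclusion.** The concern holds in limited form. As worded, {11d} and {13} give conflicting instructions on trial medication for some IVIg changes in weeks 0–18, chiefly those made for deterioration and switches after an IVIg contra-indication. Independently, {17b} includes a failure event that {12} and {30} do not, so primary-outcome status for the same regimen change can depend on whether the code was broken.

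The number of patients affected is unknown. Those open to reclassification are patients with an altered regimen who would otherwise meet the remission definition at week 52; each is worth 2.1 points of an arm of 48. The power figures above are a scale under assumed shares, not an estimate of damage. The sample size calculation stands, and the effect on the per-protocol set is confined to the listed exceptions, such as a single missed course.

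**What to change.** 1. Reconcile {11d} and {13} by stating which changes of IVIg or of other CIDP treatment each rule covers, including IVIg changes made for deterioration and IVIg discontinuation followed by a switch. Which rule applies to which change is a clinical choice for the investigators.
2. Make {30}, criterion 1 in {12}, and {17b} list the same in-treatment failure events. State whether an altered IVIg regimen counts as additional CIDP treatment, and whether unblinding by itself is a failure.
3. Issue the clarification to sites for future patients. The article reports 34 of 96 enrolled, leaving 62 at that date. For patients already treated, exposure cannot be changed, but their outcome can be classified by the same written rule, by staff unaware of allocation, before the final unblinding.

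The cost is a protocol clarification and a review of recorded deviations and unblinding forms. No new data are needed and the sample size is unchanged.
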